**9.12 Responsibility of statistics**

Statistical analyses will be supervised by [name], member of the team of the chief investigator [name]. [name] at the Dr. von Hauner Children's Hospital, Munich.

## 10 Handling of Adverse events

### 10.1 Definition

#### 10.1.1 Adverse event

The adverse event is defined as any untoward occurrence (including intercurrent diseases and accidents) in a patient or clinical investigation subject administered an investigational product and which does not necessarily have to have a causal relationship with the intervention.

Adverse events include occasions when the subjects contact the investigator or their private physicians and are examined or given medical direction. It may or may not lead to withdrawal of the subjects from the study. All adverse events occurring during the study will be reported and recorded whether or not they are considered to be non-serious or serious and related to the intervention.

#### 10.1.2 Serious adverse event

A serious adverse event is defined as any adverse event that...

- requires hospitalisation or prolongation of existing hospitalisation
- is life-threatening
- results in permanent disability / incapacity
- results in death

### 10.2 Reporting and documentation

#### 10.2.1 Reporting and documentation of adverse events (AE)

Documentation of Non-serious adverse events (AE) has to be done by the investigator on the corresponding page of the CRF during all visits and has to be classified as mild, moderate or severe (Appendix 15.12).

Documentation to include all of the following aspects:

##### 1. History

- a) Diagnosis (if available; otherwise sign or symptom)
- b) Duration (start and end date of AE)
- c) Maximum intensity (mild / moderate / severe)
- d) Frequency
- e) Outcome
- f) Coherence to intervention formula

## 2. Action taken

- a) Change of intervention (no / reduction / stop)
- b) Therapy and treatment with drugs
- c) Withdrawal

### Concerning "Outcome"

All AE must be followed until the events are resolved, the condition stabilises, the events are otherwise explained, or the subject is lost to follow-up. Indicate if the event was "recovered / resolved" or "recovered / resolved with sequelae". If the AE is ongoing at the time the subject completes the study or becomes lost to follow-up, the outcome must be recorded as "not recovered / not resolved" or "recovering / resolving". Confirm that these AE have been followed up for details of resolution.

### Concerning "Frequency"

Select either "single episode" or "intermittent".

Intermittent should be used if the subject experiences the same AE on multiple occasions over a period of time. In these circumstances, the start date will be the start date of the first episode and the end date will be the date of resolution.

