#### 7.3.5 Health observations

The paediatrician is requested to report health associated observations during the last 4 weeks (time period between the visits, reported by parents/caregivers) at each clinical study Visit. Health observations and -if used- medication must be documented in the CRF. Health observations are for example:

- nappy rash
- skin problems
- slimy stools
- infections

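### The 'intermittent' rule in section 10.2.1 can fold separate episodes of the same adverse event into one record whose duration includes symptom-free time

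*Protocol*

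**What the plan says.** Section 10.1.1 sets the completeness requirement: "All adverse events occurring during the study will be reported and recorded". Section 10.2.1 has non-serious AEs documented "on the corresponding page of the CRF during all visits". The history part of that record includes "Duration (start and end date of AE", so duration is whatever those two dates give.

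Under 'Frequency', the instruction is "Select either 'single episode' or 'intermittent", with no third option. The second code is defined as follows: "Intermittent should be used if the subject experiences the same AE on multiple occasions over a period of time". For those cases, "the start date will be the start date of the first episode and the end date will be the date of resolution".

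The text of section 10.2.1 asks for no number of episodes and no dates for each episode. It sets no longest gap beyond which a recurrence counts as new, and it does not ask whether the infant had recovered in between.

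A parallel record exists in section 7.3.5: "The paediatrician is requested to report health associated observations during the last 4 weeks". Infections are among the examples listed there.

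**The concern.** A single 'intermittent' entry suits one condition that comes and goes, such as colic or regurgitation. The rule as written is not limited to that. It can equally take in separate acute illnesses that share a name, for example colds or bouts of diarrhoea weeks apart with full recovery in between.

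Two quantities would then go wrong. The number of records would fall below the number of episodes, and the duration would include days when the infant was well. The later episodes would also lose their own onset date. That matters a little more here because the causality criteria in section 10.2.1 ask about the timing of the event relative to use of the formula.

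At stake is the safety description of a reduced-protein formula. A count that cannot exceed one per AE term per infant responds weakly to a difference in how often illness recurs. A later analysis plan cannot repair this, because the AE record itself would not hold the episode dates.

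**Working it through.** **1. What the rule does.** The protocol gives no AE rate, count or duration to reproduce, so the first step is textual. Suppose an infant has k episodes of the same AE, with episode i running from day s_i to day e_i inclusive. Reading the end date as the resolution of the last episode:

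- records kept = 1, so k − 1 episodes disappear from the record count;
- recorded duration = e_k − s_1 + 1;
- days ill = Σ(e_i − s_i + 1);
- the difference between the last two is the sum of the symptom-free gaps.

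The number of infants with at least one such AE is the same under either way of recording.

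**2. Illustration of duration (all dates assumed).** Three 3-day colds start on days 30, 70 and 110, so the last ends on day 112.

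- Under the rule: 1 record, 112 − 30 + 1 = 83 days.
- By episode: 3 records, 3 × 3 = 9 days.
- Ratio: 83/9 = 9.2.

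The ratio depends entirely on the spacing. For two 5-day episodes, counting elapsed days (end minus start):

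| Assumed episodes | Recorded | Ill | Ratio |
|---|---|---|---|
| Days 20–25 and 30–35 | 35 − 20 = 15 | 10 | 1.5 |
| Days 20–25 and 60–65 | 65 − 20 = 45 | 10 | 4.5 |
| Days 10–15 and 110–115 | 115 − 10 = 105 | 10 | 10.5 |

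**3. Illustration of counts (rate assumed).** Suppose episodes of one AE follow a Poisson law with mean m per infant, and all repeats are merged. The expected number of records per infant is 1 − exp(−m), so the share of episodes kept is (1 − exp(−m))/m.

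| m (assumed) | Share kept | Shortfall |
|---|---|---|
| 0.25 | 0.885 | 12% |
| 0.5 | 0.787 | 21% |
| 1 | 0.632 | 37% |
| 2 | 0.432 | 57% |

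If the means differ between arms, the ratio of records is (1 − exp(−m₁))/(1 − exp(−m₀)). For means of 1.5 and 1.0 the true ratio is 1.50 and the ratio of records is 0.777/0.632 = 1.23. For 1.0 and 0.5 the true ratio is 2.0 and the ratio of records is 0.632/0.393 = 1.61. With equal means the ratio stays at 1, so merging creates no false difference.

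These tables show direction and mechanism only. Nothing in the protocol says which value of m applies, and for a diagnosis that rarely recurs within 120 days the loss is small.

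**The case against.** The strongest reply is that the wording need not be read this way. 'The same AE' may mean one continuing event rather than every illness with the same diagnosis. Section 10.1.1 defines an AE as an occurrence and wants all of them recorded, so a fresh cold after recovery could be entered as a new AE. The end date is also given only as the date of resolution, not of the last resolution. This ambiguity is real. But the definition speaks of multiple occasions over time and of a first episode, so merging is the plain reading, and the text gives no criterion that would lead two investigators to code alike.

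Second, repeats are partly visible elsewhere. Health observations are taken at each visit for the preceding interval, and medication and underlying diseases go in the CRF (section 6.3.2). Diaries cover digestive symptoms for the three days before each visit. Each serious event gets its own form (section 10.2.2). In the three-cold example the colds would fall in different visit intervals. This stands as mitigation, but none of these sources is required to give a count or dates for each non-serious episode. The CRF page itself (Appendix 15.12) is not in the document, so its layout cannot be judged.

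Third, section 9 promises a description of all recorded data but defines no AE count, rate or duration analysis, and the rule is the same in both blinded arms. Both statements are correct. They limit the point to information lost and possible dilution of a difference.

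A reader might also infer a conflict with the 'Outcome' paragraph, which says "All AE must be followed until the events are resolved", on the ground that a closed event would have to be reopened when the diagnosis returns. The protocol does not say so. That paragraph covers follow-up and outcome coding and is silent on recurrence, so no contradiction is claimed.

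**Conclusion.** The point holds as a minor defect in a recording instruction. On its plain reading, section 10.2.1 turns k separate episodes of the same AE into one record and lets symptom-free time count towards duration. Episode counts and durations drawn from the AE page would be distorted, and a real difference in episode counts between arms could be diluted.

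A reader might infer that this trial's illnesses were undercounted by some stated percentage, or that the safety comparison is biased. The documents support neither. The size is unknown: the percentages above rest on an assumed Poisson mean and literal merging, and the 83-against-9-day figure rests on assumed dates. The number of infants with at least one AE, the weight-gain outcome, the sample size and the analysis populations are untouched.

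**What to change.** In section 10.2.1 and the matching CRF instruction, limit 'intermittent' to fluctuating symptoms of one continuing condition without full recovery. Require a new AE line, with its own start and end date, for each new episode after recovery.

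Amendment No. 3 shows that the intervention phase is over. For AE records already collected under the present rule, summarise the number of infants with at least one event in each arm, and do not present the duration of an 'intermittent' entry as time ill.

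The cost is one or two sentences in the protocol and CRF guidance and a few extra AE lines per infant. The reporting step needs no new data.

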### Concerning "Maximum intensity"

The maximum intensity of an adverse event is characterised as follows:

- *Mild*: short incidences which do not cause special treatment and without influence on the clinical outcome of the subject
- *Moderate*: incidences which cause mild discomfort or problems and which could influence the clinical outcome of the subject a little. The discomfort can be treated easily.
- *Severe*: incidences which cause discomfort or problems and which have to be treated with drugs or which result in a therapy.

### Concerning "Relationship to intervention"

A possible coherence between study formula and incidence has to be judged by the principal investigator. The following aspects have to be taken into consideration:

- Is there a temporal coherence between incidence and use of the study formula?
- Does a removal of study formula reduce the symptoms and do they get worse at re-introduction?
- Has the incidence been observed somewhere else, too?
- There is no coherence between incidence and other surrounding conditions, activities, or environmental factors?

Coherence between incidence and study formula is divided into:

- *no*: no coherence between incidence and study formula
- *weak*: less than 2 of the above mentioned criteria are fulfilled
- *possible*: at least 2 of the above mentioned criteria are fulfilled
- *likely*: at least 3 of the above mentioned criteria are fulfilled
- *definitely*: all 4 criteria are fulfilled

All AEs need to be followed-up. Those AEs that are not resolved until the last Visit (Visit 4) need to be documented in the AE follow up report. A copy of this report has to be sent to the monitor. A copy remains in the CRF.

### 10.2.2 Reporting and documentation of serious adverse events (SAE)

Documentation of a serious adverse event (SAE) requires that a separate Serious Adverse Event Form be completed in each case (Appendix 15.19). SAE must be reported immediately within 24 hours to the sponsor, the chief investigator and the monitor by phone and followed by faxing the filled in provided report that is part of the Serious Adverse Event Form. For the documentation it does not matter whether the incidence is associated with the study formula or not.

In addition to the above mentioned aspects for AE documentation, the documentation of a SAE includes:

- a) Age of subject
- b) Total intake of study formula on the day the SAE occurred first
- c) Seriousness (specific reason for considering event as a SAE)
  - requires hospitalisation or prolongation of existing hospitalisation
  - is life-threatening
  - results in permanent disability / incapacity
  - results in death
- d) Most likely cause of SAE
  - Disease under study
  - Others
- e) Medical comments
- f) Estimation of the Principal investigator whether there is an interrelation between the SAE and intervention, and if necessary: decision if the codes needs to be broken for this subject

All SAEs need to be followed-up, documented and follow-up needs to be reported to the sponsor, the chief investigator and the monitor.

## **11 Legal and ethical pre-requirements**

### **11.1 Legal requirements**

The study protocol will be accredited by the Ethical Committee in Belgrade / Serbia.

### **11.2 Ethical aspects**

#### **11.2.1 Protection of subject's confidentiality**

Confidentiality of all study subjects will be maintained. Codes for subject's identification will be utilized. Documents that identify the subjects beyond Subject ID Number will not be submitted to the sponsor and must be maintained in strict confidence by the investigator, except to the extent necessary to allow monitoring by the study monitor or auditing by the regulatory authorities or an independent instance ordered by the sponsor.

### **11.3 Informed consent**

The paediatrician will explain the purpose of the study in a way the parent / caregiver of potential eligible subjects are able to understand. A written information sheet in the native language of the parents / caregivers will be handed over (Appendix 15.7). All questions which will come up in the context of the study will be answered clearly and understandable. The parents of the subjects shall have sufficient opportunity to consider participation in the study. A parent of the subject cannot be led to believe that they are waiving their rights as a subject or the liability of the sponsor or investigator.

Before inclusion into the study a written informed consent has to be signed and dated by at least one parent or caregiver of the subject (Appendix 15.8) after information about the study. Single parents / caregivers need to sign without anybody else agreement. Acquisition of parent consent is the step by which subjects are enrolled into the study. Parents confirm that they have been informed properly and that the participation is voluntary. The Principal Investigator needs to point out that the parents / caregiver need to agree explicitly in taking of two blood samples. When signing the Informed consent parents / caregivers agree in taking of two blood samples (at the age of 4 or 5 days and at the age of 120 days) as mentioned explicitly on that form. Relevant information regarding the child which emerges due to the study participation will be presented to the parents / caregivers if they wish.

The informed consent has to be signed in two copies: one is kept in the subject's notes and one for the parents / caregivers.

#### **11.4 Ethics committee approval**

The study must not start before written consent is given by the Committee. If any changes or extensions are added after approval, the Ethic Committee has to be informed and approval must be given. If any severe adverse effects come up during the study period the Ethic Committee has to be informed.

#### **11.5 Declaration of Helsinki**

This study will be conducted according to the principles and rules laid down in the Declaration of Helsinki and its subsequent amendments (Appendix 15.20).

## **12 Quality assurance**

#### **12.1 GCP (Good clinical practice)**

This study will be conducted according to the principles of ICH (International Conference on Harmonization) guideline for Good Clinical Practice\* and the applicable regulatory or legal requirements. \*(<http://www.emea.europa.eu/pdfs/human/ich/013595en.pdf>)

#### **12.2 Internal Quality control**

Internal quality control will be assured by Investigator meetings (including training on the protocol at site) and regular monitoring visits.

## 13 Agreements

### 13.1 Monitoring

The monitoring will be covered by the group of [name]. [name], LMU Munich University Hospital ([name]). Monitoring needs to be conducted in accordance with the SOP for monitoring (Appendix 15.21) and in accordance with the recommendations "ICH – Note for Guidance on Good Clinical Practice" implemented in 1997 especially with Chapter 5.18 of the GCP Guidelines (ICH Topic E (6) R1 Guideline for good Clinical Practice, Step 5, Note for Guidance on Good Clinical Practice (CPMP/ICH/135/95).

During the study period a monitor will Visit the investigation group frequently and will check the Case Report Forms. The monitor will receive a study specific monitoring manual from the sponsor. The monitor starts visiting the Principal Investigator and its team before the study begins to exclude any insecurity regarding the study protocol or the procedure. In the following the monitor Visits the investigation team regularly. The monitor will check the ongoing of the study and the correct filling in of the Case Report Forms (CRFs). The CRFs will be signed by the Principal Investigator as well as by the monitor. After that they can be forwarded to the person who will be responsible for the data evaluation. At any time all data have to be available for the monitor as well as for the sponsor after request.

Recruitment progress will be checked a least every two weeks and progress needs to be reported to the sponsor.

After study initiation visit the monitor visits the site approximately every 5 weeks (~10 visits) in case recruiting proceeds as intended (recruiting terminated after 12 month).

Last Visit of the monitor will be as soon as the last child completed the study period. Every monitor Visit will be reported to the sponsor and a "Follow up" letter of identified deficiencies/mistakes, future strategies to avoid such deficiencies/mistakes and actions necessary to be taken by the site in a given time frame as mentioned in the monitoring report will be provided for the Principal investigator by the monitor. At the end of the trial the monitor will make a study closing visit to the site to ensure that all documentation is complete. Data protection issues have to be included into the monitoring.

### 13.2 Auditing

Auditors representing the sponsor may also similarly evaluate the study and its monitors. For these purposes, the Principal Investigator will make CRF and source documents available when requested.

In addition, the study may be evaluated by representatives of the national regulatory authorities, who will also be allowed access to study documents. The Principal Investigator must promptly notify the Sponsor of any audits they have scheduled with any regulatory authority.

### 13.3 Study report and publications

#### 13.3.1 Study report

After termination (“last subject out”) of the study and as soon as the statistics are done, a study report will be written by the Chief Investigator (and team) in close collaboration with the Principal Investigator and after consultation of the Sponsor (HiPP GmbH). Not later than 3 month after study termination with completed analyses the study report needs to be finalised and provided to the sponsor.

#### 13.3.2 Publications

Sponsor can use study results and reports before publication for internal purposes (including submission to the EFSA) and can cite published results without restrictions, respecting the publishers copyright. The Chief and Principal Investigator will do best efforts to publish the results in a scientific magazine.

### 13.4 Responsibilities

#### 13.4.1 Overview

|                                                               | Chief Investigator                                                                                                 | Principal Investigator                                                                                                       | Sponsor |
|---------------------------------------------------------------|--------------------------------------------------------------------------------------------------------------------|------------------------------------------------------------------------------------------------------------------------------|---------|
| Study scheduling                                       |                                                                                                                    |                                                                                                                              |         |
| Study protocol                                                |                                                                                                                    |                                                                                                                              | x       |
| Study documents                                               |                                                                                                                    |                                                                                                                              | x       |
| Subject Insurance                                             |                                                                                                                    |                                                                                                                              | x       |
| Ethical committee approval                                    |                                                                                                                    | x                                                                                                                            |         |
| Organisation                                           |                                                                                                                    |                                                                                                                              |         |
| Supply of formula and logistics to Serbia                     |                                                                                                                    |                                                                                                                              | x       |
| Logistic of formula in Serbia (store, use, dispose)           |                                                                                                                    | x                                                                                                                            |         |
| Return / destruction of unused formula + reporting to Sponsor |                                                                                                                    | x                                                                                                                            |         |
| Monitoring                                                    | x                                                                                                                  |                                                                                                                              |         |
| Conduct of the study                                          |                                                                                                                    | x                                                                                                                            |         |
| Provision of material and labels for biological samples       | x                                                                                                                  | x                                                                                                                            |         |
| Sample shipment to Munich                                     |                                                                                                                    | x                                                                                                                            |         |
| AE and SAE reporting                                          |                                                                                                                    | x                                                                                                                            |         |
| Data management                                               | x                                                                                                                  | x                                                                                                                            |         |
| Retention of records                                          | x                                                                                                                  | x                                                                                                                            | x       |
| Laboratory analysis                                           | 
 
Plasma amino acid profiling
 
Plasma fatty acid profiling
 
 | Full Blood count with differential, CRP, Astrup, Electrolytes, Glucose, Serum albumin, Serum creatinine, Blood urea nitrogen |         |
| Statistics                                                    | x                                                                                                                  |                                                                                                                              |         |
| Final study report                                            | x                                                                                                                  | x                                                                                                                            |         |
| Publication                                                   | x                                                                                                                  | x                                                                                                                            |         |

